#### Data reliability

To ensure data quality, a random 5% of resident charts at each time period will be abstracted by a second data collector, with inter-rater reliability calculated using kappa. Refresher training will be completed if kappa falls below 0.7 for any measure.

#### Measures

The measures and the time points at which these will be collected are summarized in Table 4[79,17,30-93] (Complexity Science Measures) and Table 3 (Fall-related measures). In addition, data will be collected about each nursing home, including bed size, nursing staff hours. Chain and religious affiliation will be collected from publicly available sources http://www.nhcompare.gov. Nursing staff turnover during the intervention period will be obtained from administrators. These data will be used as covariates in the multivariable outcomes analyses. All measures will be aggregated to the cluster level of the facility.

**Table 4 T4:** Complexity science measures

Concept Measured; Source	Psychometrics; Calculation
Demographics; self-report	Age, sex, job title, years in position, education, and ethnicity (collected at baseline or at enrollment into the study. Categorical measurement)

Communication patterns; all staff	Mean scores on Roberts and O'Reilly openness, accuracy scales [79] and Shortell's timeliness scale [80,81]. The scales show adequate reliability and validity in various settings [79,80,82]. In our preliminary studies scales showed reliability alphas of 0.81, 0.72 and 0.68, respectively; construct validity confirmed by factor analysis and hypothesis testing [17,30,83].

NA and LPN participation in decision making about resident care; all staff	Mean score on Anderson et al.'s [83] Participation in Decision-making Instrument (PDMI). The PDMI is established with demonstrated reliability in nursing homes [17,18,83-85] and construct validity established through factor analysis [83] and hypothesis testing [17,84,86]. Nursing home samples achieved alpha coefficients of > 0.90.

Relational Coordination; all staff	Mean scores on Gittell's [87] five-point scale on which staff will rate interactions between groups (e.g., NA to nurse, NA to dietary; nurse to MD). Three aspects are measured including: frequency of communication; high-quality communication; and supportive relationships [88,89]. Gittell [88] adapted this scale for nursing homes and achieved a one factor scale and a Chronbach's alpha 0.86. In our preliminary study, we achieved an alpha of 0.95 on a sample of nursing home staff.

Psychological Safety; All staff	Three items from Edmondson's 7-point psychological safety scale that were modified for heath care [90]. The items ask about whether people are comfortable checking with each other or asking questions, whether people value others' unique skills and talents, and whether people are able to bring up problems and tough issues [91]. Studies in healthcare settings reported alphas of 0.74 [91] and 0.73 [92] We slightly revised the scale by changing the word 'unit' to 'nursing home. Because the scale has not been used in a nursing home sample previously we tested the reading level and found that it read at the 6th grade level, which is acceptable for this low literacy sample.

Safety organizing scale; all staff participants	Mean score on Vogus and Sutcliff's scale designed to measure five 'interrelated behavioral processes: preoccupation with failure, reluctance to simplify interpretations, sensitivity to operations, commitment to resilience, and deference to expertise' [93, p. 47]. In a large sample of hospital RNs, the 9-item, 7-point scale showed reliability (alpha = 0.88), convergent and discriminant validity, and criterion validity, and was reliability aggregated to reflect a unit-level construct [93]. We revised the wording for nursing homes. Alphas were > 0.90 in both the baseline and follow up survey in our preliminary studies.

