**Methods/design:**

Sixteen nursing homes will be randomized to one of two study arms, CONNECT + FALLS or FALLS alone. Subjects (staff and residents) are clustered within nursing homes because the intervention addresses social processes and thus must be delivered within the social context, rather than to individuals. Nursing homes randomized to CONNECT + FALLS will receive three months of CONNECT first, followed by three months of FALLS. Nursing homes randomized to FALLS alone receive three months of FALLs QI and are offered CONNECT after data collection is completed. Complexity science measures, which reflect staff perceptions of communication, safety climate, and care quality, will be collected from staff at baseline, three months after, and six months after baseline to evaluate immediate and sustained impacts. FALLS measures including quality indicators (process measures) and fall rates will be collected for the six months prior to baseline and the six months after the end of the intervention. Analysis will use a three-level mixed model.

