CONNECT is a multi-component intervention that helps staff: learn new strategies to improve day-to-day interactions; establish relationship networks for creative problem solving; and sustain newly acquired interaction behaviors through mentorship. Complexity science and empirical research suggest that interaction patterns determine information flow, knowledge transfer, and capacity to monitor behaviors in healthcare settings [16,18,30]. In a preliminary test of CONNECT, we found support for the hypothesis that the intervention would improve staff interactions and reduce falls [31]. We propose that CONNECT, when combined with a content focused falls QI program (FALLS), will result in better resident outcomes when compared to FALLS alone. We chose falls for this test of CONNECT because: falls rates are high in nursing homes [32,33]; accepted practice guidelines and fall prevention programs exist [34-37]; and there is ample evidence from efficacy trials that multi-factorial risk reduction interventions reduce fall rates [3-5,13,38].

The study aims are to:

1. Compare the impact of the CONNECT intervention plus a falls reduction QI intervention (CONNECT + FALLS) to the falls reduction QI intervention alone (FALLS) on fall-related process measures in nursing home residents.

2. Compare the impact of CONNECT + FALLS to FALLS alone on fall-rates in nursing home residents, and determine whether these are mediated by the change in fall-related process measures.

3. Compare the impact of CONNECT + FALLS to FALLS alone on complexity science measures as reported by nursing home staff and determine whether these mediate the impact on fall-related process measures and fall rates.

To complete these aims we will use a cluster randomized, controlled trial design with the facility-level change in fall and complexity science measures as the primary outcomes. Because the CONNECT and FALLS interventions both encourage facility-wide change in staff behavior, randomization will occur at the facility level and subjects (nursing home staff and residents) are clustered within homes.

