### Risks and challenges

A major challenge for nursing home research is the potential for staff turnover. Using a successful strategy from our prior studies, we will secure a written commitment from the nursing home administrator, director of nursing, and if relevant, a corporate representative, that the study will continue even if one or more top administrators leave. We also have designed this study to be robust to staff turnover by incorporating the CONNECT in-class learning sessions into the nursing home's orientation for new staff. Exploratory analyses will determine whether staff turnover affects the fall-related processes or fall rate measures. Another challenge for nursing home research is designing approaches that are appropriate and acceptable for all levels of staff, regardless of education and socio-economic background. We use storytelling, which is an efficient yet high-impact method of conveying information, infused with relevant nursing home cultural norms, values, and beliefs [72]. Because storytelling and role play are based on descriptive verse, they may attenuate learning barriers associated with low literacy and English as a second language [73].

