### The interventions

CONNECT will be implemented over 12 weeks, followed by FALLS for an additional 12 weeks. The FALLS intervention is a modification of interventions previously tested by the PI [7,69] and is based on the Falls Management Program developed by the Agency for Healthcare Research and Quality [59,74]. Details of the intervention components, rationale, participants, and time required for CONNECT and FALLS are in Tables 1[75] and 2[75] respectively. All aspects of the interventions are applied to cluster level; even aspects that are delivered to individuals, address cluster level interactions. The complete text of the CONNECT and FALLS protocols are available on request to the authors.

**Table 1 T1:** CONNECT protocol activities, rationale, who is involved and time required

CONNECT Protocols	Rationale/Outcome	Who	Time

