##### H2C

Intervention-related improvements in fall rates and injurious falls will be mediated by improvements in fall-related process measures.

The dependent variables for H2a and H2b will consist of one Poisson distributed outcome (fall rates), and one dichotomous outcome (the probability of a recurrent fall). For fall rates, we will use PROC GLIMMIX to re-estimate the model with fall rates dependent and intervention group, time, and relevant covariates as predictors, using the same analysis as for Aim 1. To test H2c, we will add the process measures (from Aim 1) to the models for H2a and H2b as time-changing predictors. We will use bootstrap methods [95] to test significance of these indirect effects.

#### Aim 3

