##### H3A

Staff in facilities randomized to receive CONNECT + FALLS will report significantly greater improvement from baseline immediately and three months after the intervention than staff in facilities receiving FALLS alone on complexity science measures of: communication openness, accuracy and timeliness; participation in decision making; relational coordination; psychological safety; and safety culture.

For these outcomes, we will use PROC MIXED to estimate a mixed model to estimates the effect of the intervention on each outcome averaged over time.

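### Staff turnover during the intervention period, measured after randomisation, is planned as a covariate in the outcome models and can distort the arm effect where that effect is a between-home contrast

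*Protocol article*

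**What the plan says.** The Measures section lists home-level data to be collected and ends: "Nursing staff turnover during the intervention period will be obtained from administrators. These data will be used as covariates in the multivariable outcomes analyses". Nothing in the article limits the covariate to turnover before baseline, defines the window, or gives the unit (a cumulative percentage or a rate per month).

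The covariates enter the main models. For fall rates, the Aim 2 analysis text states: "we will use PROC GLIMMIX to re-estimate the model with fall rates dependent and intervention group, time, and relevant covariates as predictors". For the staff measures, the H3A text describes a mixed model that "estimates the effect of the intervention on each outcome averaged over time".

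The arms differ in length of intervention. The abstract's Methods/design paragraph says: "Nursing homes randomized to CONNECT + FALLS will receive three months of CONNECT first, followed by three months of FALLS", and then: "Nursing homes randomized to FALLS alone receive three months of FALLs QI and are offered CONNECT after data collection is completed". The section The interventions gives the same in weeks: "CONNECT will be implemented over 12 weeks, followed by FALLS for an additional 12 weeks".

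Turnover has a second, separate role in Risks and challenges: "Exploratory analyses will determine whether staff turnover affects the fall-related processes or fall rate measures". It is not among the mediators named in H2C or H3B.

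**The concern.** H2A, H2B and H3A ask for the total effect of assigning a home to CONNECT + FALLS rather than FALLS alone. A covariate measured after assignment is safe in such a model only if assignment does not affect it, directly or through the way it is measured. Here both routes are open.

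- **Through the intervention.** The Background says that CONNECT helps staff "establish relationship networks for creative problem solving; and sustain newly acquired interaction behaviors through mentorship". A programme that changes working relationships could change who stays. If it does, conditioning on turnover takes out whatever part of the effect runs through retention.
- **Through the measurement window.** If turnover is counted over each home's own intervention period, the CONNECT + FALLS homes have twice as long to accrue it. The covariate then carries information on arm even if CONNECT leaves retention untouched.

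With 16 homes, a covariate that competes with the arm indicator can be costly in precision, and the resulting bias can run towards or away from the null.

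**Working it through.** The plan gives no figure to reproduce: this is a choice of covariate, and the article reports no turnover rate, spread, or link to falls. Every size below therefore rests on assumed values.

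**1. Window.** CONNECT + FALLS: 12 + 12 = 24 weeks. FALLS alone: 12 weeks. Ratio 24/12 = 2.0, if the period is each home's own.

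**2. Effect removed if CONNECT changes turnover.** Take the 23% difference in fall rate from Statistical power as the true total effect: ln 0.77 = −0.261. If a share m runs through turnover, the adjusted arm effect in a between-home model is exp(−0.261 × (1 − m)).

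- m = 0.10: exp(−0.235) = 0.79
- m = 0.25: exp(−0.196) = 0.82
- m = 0.50: exp(−0.131) = 0.88

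A simulation of 8 v 8 homes (4,000 replicates) gave the same three values; without the adjustment the estimate stayed at 0.77.

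**3. Bias from unequal windows alone.** Assume CONNECT does not change turnover, the monthly rate averages 4% in both arms, the log fall rate rises by 5 per unit of monthly rate, and cumulative turnover is entered (3 v 6 months).

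- Mean cumulative turnover: 0.12 v 0.24, a difference of 0.12.
- Pooled within-arm slope of log fall rate on cumulative turnover: 5 × (3 + 6)/(3² + 6²) = 5 × 9/45 = 1.0.
- Shift in the arm effect: −1.0 × 0.12 = −0.12.
- A true null becomes exp(−0.12) = 0.89; a true 0.77 becomes exp(−0.261 − 0.12) = 0.68.

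The simulation (between-home coefficient of variation 0.4, residual SD 0.2) gave 0.88 and 0.68. The SD of the estimate rose from 0.108 to 0.140, a factor of 1.30.

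**4. Precision lost if a cumulative figure is entered.** With d the arm difference in mean turnover and s the between-home SD (percentage points), r² = (d/2)²/((d/2)² + s²), VIF = 1/(1 − r²), and the SE multiplier is √VIF. Annual turnover of 50% gives 25 v 12.5 points (d = 12.5); 25% gives 12.5 v 6.25 (d = 6.25).

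| d | s | r² | VIF | SE multiplier |
|---|---|---|---|---|
| 12.5 | 3 | 0.81 | 5.34 | 2.31 |
| 12.5 | 5 | 0.61 | 2.56 | 1.60 |
| 6.25 | 12 | 0.06 | 1.07 | 1.03 |

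The table uses one SD for both arms. If the SD doubles with the window (5 and 10), the mean variance is (25 + 100)/2 = 62.5, r² = 39.1/101.6 = 0.38 and the multiplier is 1.27; with 3 and 6 it is 1.65. Simulating monthly rates with coefficients of variation of 0.3, 0.5 and 1.0 gave about 1.5, 1.2 and 1.07.

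**5. Which models are exposed.**

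- *Between-home contrasts* (H3A averaged over time; H2B in the post-intervention period; fall rates with group and time but no interaction): steps 2 to 4 apply.
- *Group-by-time contrast*: in a balanced linear example, adding turnover as a main effect left the interaction coefficient at 1.3667, the same as without it.
- *Cluster as a fixed effect*, as Statistical power states: 16 home indicators plus time and arm-by-time make 18 columns of rank 18. Adding arm and turnover makes 20 columns, still of rank 18. One turnover value per home cannot be estimated.

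**The case against.** The strongest reply is that the planned models are largely immune. The Background names facility-level change as the primary outcome, H1A and H1B are comparisons of change, and the Aim 2 text says fall rates will be analysed as in Aim 1. If all of these are group-by-time contrasts, a home-level main effect does little. If cluster is fixed, the covariate drops out. This stands, and it rules out a reading that a colleague might be tempted by: that every adjusted arm effect in the trial ceases to estimate the effect of assignment. It does not clear H3A, H2B, or the Aim 2 model as listed, which has group, time and covariates. The fixed-cluster route does not rescue the covariate either; it makes it unusable.

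Four further points are fair:

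- The article does not say that CONNECT changes turnover. Risks and challenges treats turnover as an external difficulty to which the design should be robust. The effect is an inference from what CONNECT targets.
- The doubled accrual time is the plain reading of the stated durations, but the window and unit are undefined. A monthly rate or a common window would remove the length artefact, though the variable would still be post-randomisation.
- A reader might also infer collider bias. That needs an unmeasured common cause of turnover and outcome, and the article identifies none.
- The variance-inflation formula ignores any residual variance that turnover explains, so it is not the net change in the standard error.

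**Conclusion.** The concern holds in a conditional form. It is explicit in the article that a variable measured after randomisation will adjust the outcome models, and nothing restricts it to a baseline value. In the between-home analyses this can remove part of the total effect or bias it. Under the assumptions shown, a rate ratio of 0.77 could be reported as anything from 0.68 to 0.88, and a true null as about 0.88. If a cumulative figure over each home's own period is used, the standard error multiplier is about 1.03 to 2.3. That range runs from negligible to severe because turnover and its spread are assumed, so no single value in it should be quoted as the expected loss.

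In group-by-time analyses the covariate does little harm and little good. With cluster fixed, it conflicts with the model. On none of these readings does it help to estimate the effect of assignment. The documents do not support saying that CONNECT will change turnover, or that all outcome models are biased.

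**What to change.** Amend the Measures section so that intervention-period turnover is not a covariate in the main outcome models. If adjustment for turnover is wanted, collect it from administrators for the six months before baseline, which matches the abstraction window already used for the fall measures. Keep intervention-period turnover only for the exploratory analysis in Risks and challenges, as a monthly rate or over a window common to both arms.

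The cost is a change to one sentence and one extra baseline item per home. The other covariates fixed before randomisation, such as bed size and chain or religious affiliation, do not share this problem and need no limit on this account.

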### Fall measures

#### Fall risk factor reduction indicators

Measures chosen for this study are: a component of previous efficacy trials and fall clinical practice guidelines; found to be reliably measured by chart abstraction in previous studies [7,9]; and included in the educational components of the FALLS intervention. These indicators were previously found to be sensitive to change, and not impacted by a ceiling effect [7]. We will calculate the proportion of fallers with medical record evidence of the fall risk reduction indicator, and determine indicator counts for each resident. Timing of the risk factor reduction will be recorded as: within 48 hrs of a fall, within one month of a fall, during the six-month abstraction period. Definitions are found in Table 3.

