### Analysis

The study hypotheses pertain to the cluster level of the nursing homes. Hierarchical linear modeling with Glimmix was used to account for clustering in this study. This procedure is useful when there are multi-level, nested sources of variability such as patients and staff clustering within nursing homes. The Glimmix procedure analyzes both individual and group level trajectories of change over time. Our hypotheses (H) to address the study aims and related analysis are listed below.

#### Aim 1

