##### H1B

Residents in facilities randomized to receive CONNECT + FALLS will have greater improvements in fall risk factor intervention counts from the six-month period preceding the intervention (baseline) to the six-month period after the intervention (follow-up), compared to similar residents in facilities receiving FALLS alone.

As the dependent variables for H1a and H1b are counts, we will use PROC GLIMMIX to estimate the models. A significant negative coefficient will indicate that the intervention reduced fall rates. As is standard practice with Poisson models, we will test for over dispersion in initial analyses and employ a negative-binomial model if over dispersion is present.

#### Aim 2

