##### H3B

Improvements in fall-related process measures and fall-related outcome measures will be mediated by changes in complexity science measures.

To test H3B, we will calculate nursing home-level means on the complexity science measures, add these mean as time-changing predictors to our models (above) predicting fall-related process and outcome measures. We will use bootstrap methods [95] for testing the significance of these indirect effects.

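### The unit of analysis is contradictory: all measures are to be aggregated to the facility, yet the models and the power use individual residents and staff, and the choice affects the type I error

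*Protocol article*

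**What the plan says.** All places are in the protocol article.

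**Pointing to the facility.**
- Measures: "All measures will be aggregated to the cluster level of the facility".
- Background, after the study aims: the trial takes "facility-level change in fall and complexity science measures as the primary outcomes".
- Analysis, opening: "The study hypotheses pertain to the cluster level of the nursing homes".
- Table 3: the fall rate has occupied bed-days as its denominator, and recurrent falling is defined as a proportion of residents. Both are group quantities.

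**Pointing to the individual.**
- Fall risk factor reduction indicators: the team will "determine indicator counts for each resident". The same sentence also plans the proportion of fallers meeting each indicator.
- H1B: "As the dependent variables for H1a and H1b are counts, we will use PROC GLIMMIX to estimate the models". A Poisson model is replaced by a negative binomial one if over-dispersion is found.
- H2C: recurrent falling is "one dichotomous outcome (the probability of a recurrent fall").
- Abstract, Methods/design: "Analysis will use a three-level mixed model".
- Statistical power: the power for Aim 2 is attributed to the resident sample, and staff attrition enters the calculation. Cluster is to be a fixed effect, and correlation within homes is declared unnecessary.

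**A special case.** Under H3B, for the mediation analysis, "we will calculate nursing home-level means on the complexity science measures". That step would be redundant if every measure had already been aggregated.

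**The concern.** Read literally, the Measures sentence leaves 16 values per outcome and period. No resident or staff level then remains for a three-level model. A facility mean is not a count, and a facility proportion is not a yes/no outcome. The article does not say whether the aggregate is a mean, a total with an exposure term, or events out of trials, nor how it enters the model.

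This is more than a detail left to an analysis plan, because the article states both sides. The readings differ in standard error, degrees of freedom and type I error. An analyst could follow either and claim to have kept to the protocol.

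**Working it through.** **Inputs from the article.** 16 homes; 50 sampled residents per home (800 in all); 40% recurrent fallers; a 23% difference in recurrent falling at 80% power; a 15% difference for Aim 1; two-sided 0.05; cluster as a fixed effect.

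**Assumptions.** 8 homes per arm; 50 residents per home and period; mean indicator count 3; 23% and 15% taken as relative differences; all ICCs. The article gives none of these.

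**1. Which reading does the stated power belong to?** Take 0.40 against 0.40 × 0.77 = 0.308, with 400 independent residents per arm.
- Variance sum: 0.40 × 0.60 + 0.308 × 0.692 = 0.4531.
- SE = √(0.4531/400) = 0.0337; 0.092/0.0337 = 2.73.
- Power = Φ(2.73 − 1.96) = 78.0% (77.8% with pooled variance).

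The stated 80% therefore comes back, marginally, from resident-level data without clustering. Eight against eight facility proportions, tested on 14 df, give 72% even at ICC 0.

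**2. What does correct aggregation cost?** Recurrent falls, m = 50, design effect 1 + 49 × ICC, comparing follow-up values:

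| Assumed ICC | Resident level, design effect applied | 8 v 8 facility proportions, 14 df |
|---|---|---|
| 0 | 78% | 72% |
| 0.01 | 61% | 55% |
| 0.02 | 49% | 44% |
| 0.05 | 31% | 28% |
| 0.10 | 20% | 18% |

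The cost is 2 to 6 points. The standard error is essentially the same in both columns, so the gap comes almost wholly from using a t distribution on 14 df instead of the normal. The fall down the table is due to between-home variation and occurs under either unit.

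**3. Type I error with fixed home effects.** A fixed home effect removes stable differences between homes. It does not remove a home's own drift between the two periods. Let ρ be the home-by-period share of variance. The true variance of the arm-by-period contrast exceeds the model's by about D = 1 + mρ/(1 − ρ), and the actual error is 2[1 − Φ(1.96/√D)]. With m = 50:
- ρ = 0.01: D = 1.505, 1.96/√D = 1.60, error 11%.
- ρ = 0.02: D = 2.02, 1.96/√D = 1.38, error 17%.
- ρ = 0.05: D = 3.63, 1.96/√D = 1.03, error 30%.

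Simulations agree: 11%, 16% and 30% for Poisson resident rows, and 11%, 18% and 32% for normal data with an added home variance share of 0.05. Poisson home totals with an exposure term carry the same likelihood for the intervention effect, so they share the problem. A t-test on the 16 home-level changes gave 4.9% to 5.4% in simulation.

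The article does not make clear whether the 50 residents are per period or span both. If both, m = 25 and the same formula gives D = 1.25, 1.51 and 2.32, and errors of 8%, 11% and 20%.

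**4. Facility means entered as single Poisson observations.** A mean of 50 Poisson counts has variance μ/50, but the likelihood assigns it μ. The standard error is √50 = 7.1 times too large. With μ = 3 and follow-up values only, the model SE of the log rate ratio is √(1/24 + 1/27.6) = 0.279. The correct value without between-home variation is 0.279/7.07 = 0.039. Significance needs an estimate beyond 1.96 × 0.279 = 0.547, against a true log(1.15) = 0.140. In simulation (4,000 trials), rejection was 0.0% under the null and 0.0% at a 15% effect. Such data look under-dispersed, and the planned check looks only for over-dispersion.

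**The case against.** The best defence is that the Measures sentence states the level of inference and the Analysis section governs the models. The Background and Analysis sections do place outcomes and hypotheses at facility level, and the Analysis section says the procedure handles individual as well as group trajectories. How an aggregate enters the model may fairly be left to a fuller document. Aggregated does not mean averaged: totals remain counts, and a proportion can be modelled as events out of trials. This shows that aggregation can be reconciled with count and binary models. It does not restore a resident level to aggregated data, explain why H3B needs its own averaging step, or match the power section.

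A reader might infer that the plan, applied as written, yields wrong error bars and almost no power. The documents do not support that. It follows only from step 4, and no section specifies unweighted means in a Poisson or binary likelihood. Nor is the fall rate the only facility-level outcome, since Table 3 also defines recurrent falling as a proportion.

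On step 3, the planned negative binomial switch could absorb some home-by-period variation in home totals. For resident rows it models spread between residents and still treats those in the same home and period as independent. If the three-level model includes a home-by-period term, the inflation is addressed, but the abstract does not name its levels and the power section makes cluster fixed.

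**Conclusion.** The contradiction stands, and the article should be corrected. Aggregation itself is not the danger: done properly it is valid and costs about 2 to 6 points of power. The danger is that the unit is left open next to a fixed home effect. Under one permitted reading, the type I error is about 11%, 17% or 30% at home-by-period ICCs of 0.01, 0.02 or 0.05; under another it stays near 5%. The inflation rests on assumed ICCs and on 50 residents per home and period; at 25 it is 8%, 11% and 20%, and with no home-by-period variation there is none. The sevenfold standard error is a possible misreading, not the plan. The neglect of between-home variation in the power calculation is a problem of the Statistical power section under either unit.

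**What to change.** Replace the aggregation sentence in Measures with one unit per outcome:
- H1A, H1B and H2B: the resident.
- H3A: the staff respondent.
- H2A: falls per facility and period, with occupied bed-days as exposure.
- H3B: home-level means, for the mediators only.

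Include home-by-period variation in each model, with small-sample degrees of freedom. Alternatively, analyse the 16 home-level changes with a t-based method on 14 df.

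Then bring the rest of the article into line: the abstract's three-level model (name the levels), the primary-outcome statement in Background, Table 3, the indicator section, the Analysis opening, H1B, H2C and Statistical power. The last needs more than wording, because its fixed-cluster statement and its reason for omitting correlation within homes cannot stay as they are, and the power must be recalculated over a stated range of ICCs.

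Data collection does not change. The cost is a revised analysis text and less favourable stated power: for recurrent falls, comparing follow-up values on 14 df, 55% at an assumed ICC of 0.01 and 44% at 0.02, against the 80% now claimed.
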